### Research Objectives and Hypotheses

The purpose of this article is to present the PsicoFIT protocol, detailing its design, implementation, and evaluation plan to guide the intervention. This protocol is embedded within a broader study, whose overall goal is to examine changes resulting from a psychoeducational intervention delivered in the face-to-face and semi face-to-face modalities among sedentary, overweight adults who are supporters of a football club, as well as to evaluate the mediating effects of psychological mechanisms, the moderating effects of each participation modality, and the intervention’s acceptability and perceived contribution by the participants.

To guide the development of this protocol, the following specific objectives and corresponding hypotheses were defined, forming part of the comprehensive study design to be examined in subsequent publications once the intervention has been implemented.

Specific Objective 1. To examine the associations between the coach’s controlling interpersonal style, basic psychological need satisfaction, autonomous motivation, healthy lifestyle, and burnout in the face-to-face and semi face-to-face modalities, both at baseline and post-intervention.

**Hypothesis** **1.**
*The coach’s controlling interpersonal style will be negatively associated with basic psychological need satisfaction. In turn, basic psychological need satisfaction will be positively associated with autonomous motivation. Autonomous motivation will be positively associated with healthy lifestyle and negatively associated with burnout in both the face-to-face and semi face-to-face modalities, both at baseline and post-intervention.*

Specific Objective 2. To examine changes in the coach’s controlling interpersonal style, basic psychological need satisfaction, autonomous motivation, healthy lifestyle, and burnout both at baseline and after the psychoeducational intervention, and to compare these changes between the face-to-face and semi face-to-face modalities.

**Hypothesis** **2.**
*Significant changes in the coach’s controlling interpersonal style, basic psychological need satisfaction, autonomous motivation, healthy lifestyle, and burnout are expected at post-intervention compared to baseline. Additionally, the magnitude of these changes may differ between the face-to-face and semi face-to-face modalities.*

Specific Objective 3a. To evaluate the mediating effect of the satisfaction of basic psychological needs and autonomous motivation between the coach’s controlling interpersonal style and healthy lifestyle (mediating effect 1), as well as between the coach’s controlling interpersonal style and burnout (mediating effect 2) in both the face-to-face and semi face-to-face modalities, at baseline and post-intervention.

**Hypothesis** **3a1.**
*Basic psychological need satisfaction and autonomous motivation will mediate the relationship between the coach’s controlling interpersonal style and healthy lifestyle in both the face-to-face and semi face-to-face modalities, at baseline and post-intervention.*

**Hypothesis** **3a2.**
*Basic psychological need satisfaction and autonomous motivation will mediate the relationship between the coach’s controlling interpersonal style and burnout in both the face-to-face and semi face-to-face modalities, at baseline and post-intervention.*

Specific Objective 3b. To evaluate the mediating effect of autonomous motivation between basic psychological need satisfaction and healthy lifestyle (mediating effect 3), as well as between basic psychological needs satisfaction and burnout (mediating effect 4), in both the face-to-face and semi face-to-face modalities, at baseline and post-intervention.

**Hypothesis** **3b1.**
*Autonomous motivation will mediate the relationship between basic psychological need satisfaction and healthy lifestyle in both the face-to-face and semi face-to-face modalities, at baseline and post-intervention.*

**Hypothesis** **3b2.**
*Autonomous motivation will mediate the relationship between basic psychological need satisfaction and burnout in both the face-to-face and semi face-to-face modalities, at baseline and post-intervention.*

Specific Objective 4. To evaluate the moderating effects of the type of participation (face-to-face and semi face-to-face) both at baseline and after the intervention as follows: (a) the relationship between the coach’s controlling interpersonal style and basic psychological need satisfaction (moderating effect 1); (b) the relationship between basic psychological need satisfaction and autonomous motivation (moderating effect 2); (c) the relationship between autonomous motivation and healthy lifestyle (moderating effect 3); and (d) the relationship between autonomous motivation and burnout (moderating effect 4).

**Hypothesis** **4.**
*The type of participation (face-to-face and semi face-to-face) will moderate the relationships between the following both at baseline and after the intervention: (a) the coach’s controlling interpersonal style and basic psychological need satisfaction; (b) basic psychological need satisfaction and autonomous motivation; (c) autonomous motivation and healthy lifestyle; and (d) autonomous motivation and burnout.*

Specific Objective 5. To analyze the acceptability of the PsicoFIT intervention and the perceived contribution by participants in terms of motivation toward physical activity, psychological well-being, and psychological ill-being in both the face-to-face and semi face-to-face modalities.

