## 2. Materials and Methods

### 2.1. Design

A mixed-methods convergent parallel approach will be adopted [40] within the framework of a longitudinal comparative pragmatic clinical trial [41]. To examine changes and to compare delivery modalities, the participants will be randomly assigned to receive the intervention in either a face-to-face or semi face-to-face modality, with measurements at time 1 (baseline) and time 2 (post-intervention).

Quantitative analyses will include hierarchical multiple regression analyses, pre-post comparisons, and regression-based mediation and moderation analyses [42,43]. Additionally, the acceptability and perceived contribution of the intervention will be explored using a qualitative phenomenological approach [44] through a post-intervention focus group. The findings from the statistical analysis and the results of the phenomenological analysis will be integrated, allowing for a more precise understanding of the intervention’s evaluation, its perceived impact, and the acceptability of each modality.

Although this study does not constitute a controlled trial and does not include a no-intervention control group, to ensure methodological rigor and scientific transparency, it has been designed in accordance with the standard items of the SPIRIT 2013 Statement for clinical trial protocols [45] (see Supplementary Materials S1) and takes as a reference the elements of the Trials Registration Data Set (TRDS) [46] considered by the World Health Organization (WHO). In addition, the description of the intervention has been guided by the Template for Intervention Description and Replication (TIDieR) checklist [47] (see Supplementary Materials S2), with the aim of providing a comprehensive, transparent, and replicable account of the intervention components, delivery procedures, materials, and implementation context.

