#### 2.2.4. Sample Size and Randomization

The study will employ a non-probabilistic convenience sampling [44], including participants who meet the established inclusion criteria and are available during the recruitment period.

The sample size (*n* = 80) was determined pragmatically and based on operational feasibility, considering the resources and organizational requirements of the intervention, including the facilitators’ capacity, the availability of staff responsible for implementation, the total program duration, and the estimated recruitment period.

The participants will be distributed equally between the two intervention modalities, with 40 participants per modality (20 men and 20 women in each; see Table 1).

Randomization will be conducted using a computer-generated procedure, applying stratification to ensure an equitable distribution between the groups. The randomization will be generated and safeguarded by a researcher independent of the intervention. Once the assignment is generated, each participant will be notified individually.

Blinding of the participants and facilitators is not feasible due to the nature of the intervention delivery format. The face-to-face and semi face-to-face modalities differ in observable aspects, such as the type of interaction, communication channels, and module dynamics, making it impossible to conceal the assigned modality. Nevertheless, participants will not receive information regarding the activities or specific structure of the alternative modality. Likewise, facilitators will necessarily be aware of the format of the modality they deliver.

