#### 2.3.3. Assessment Timeline

Evaluations will be conducted at the following times:Time 1. Week 0: What is My Lifestyle Like? Survey.Time 1. Week 2: Controlling Coach Behaviors Scale, Perceived Autonomy in Sport Scale, Perceived Competence Scale, Need for Relatedness Scale, Sport Motivation Scale II, and Athlete Burnout Questionnaire. The questionnaires will be administered at this point because they will assess the variables that require the participants to have previously interacted with the program components in order to be appropriately perceived.Time 2. Week 13: All instruments and the focus group will be administered.

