### 2.6. Data Analysis

#### 2.6.1. Quantitative Analysis

Due to the practical limitations in following up with those participants who do not complete the program, the primary analysis will be conducted using a per-protocol approach [111], considering only those participants with complete data at baseline and at the end of the intervention; missing data will not be imputed.

This approach will allow for evaluating the changes associated with each intervention under real-world implementation conditions, acknowledging the anticipated risk of participant attrition and that the benefits of randomization may not be fully preserved, while reflecting its applicability in a pragmatic context.

All statistical analyses will consider a 95% confidence level (5% error), ensuring transparency and reproducibility.

Preliminary Analysis. Descriptive statistics for central tendency (mean, median), dispersion (standard deviation and variance), and distribution (skewness and kurtosis) will be estimated for each observed variable. Next, normality tests will be conducted, and the reliability of the instruments will be estimated by measuring their internal consistency through Cronbach’s alpha (α) and McDonald’s omega (ω) coefficients. Subsequently, bivariate correlation analyses will be performed to measure the strength and direction of the relationship between the variables.

Associations among motivational and outcome variables. To examine the associations between the coach’s controlling interpersonal style, basic psychological need satisfaction, autonomous motivation, healthy lifestyle, and burnout, hierarchical multiple regression analyses will be conducted. Separate models will be estimated for each intervention modality (face-to-face and semi face-to-face) and for each measurement occasion (baseline and post-intervention), with predictor variables entered in a theoretically driven manner [42]. Effect sizes and confidence intervals will be calculated to complement the statistical significance, and statistical power will be considered when interpreting the results [112].

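### Hypothesis 4 predicts moderation by the randomised modality at baseline; that half cannot be interpreted as stated, because most Time 1 scores come from week 2 of delivery

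*Protocol article*

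**What the plan says.** Objective 4 and Hypothesis 4 concern four relationships: (a) coach's controlling style with need satisfaction, (b) need satisfaction with autonomous motivation, (c) autonomous motivation with healthy lifestyle, and (d) autonomous motivation with burnout. The hypothesis is that type of participation "will moderate the relationships between the following both at baseline and after the intervention".

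Modality is a randomised factor. Section 2.1 says "the participants will be randomly assigned to receive the intervention in either a face-to-face or semi face-to-face modality", and calls Time 1 the baseline. Section 2.6.1 (Moderation Effects) applies interaction terms to pre- and post-intervention data. It reads a significant interaction as showing that the relationship differs by modality, with no separate reading for Time 1. It labels moderation exploratory.

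The timetable in section 2.3.3 splits Time 1 in two. Lifestyle comes first: "Time 1. Week 0: What is My Lifestyle Like? Survey". The rest follow: "Time 1. Week 2: Controlling Coach Behaviors Scale, Perceived Autonomy in Sport Scale, Perceived Competence Scale, Need for Relatedness Scale, Sport Motivation Scale II, and" the Athlete Burnout Questionnaire. The stated reason is that "they will assess the variables that require the participants to have previously interacted with the program components in order to be appropriately perceived". Table 1 places allocation before week 0 and shows both interventions running from week 1 to week 12.

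**The concern.** A factor assigned at random cannot alter how variables relate to each other before anyone has been exposed to it. A hypothesis that it does so at baseline is either false under randomisation or refers to a measurement that is not a baseline. The article calls Time 1 a baseline and schedules most of it after exposure has begun.

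The stake is what may be concluded. Under the reading rule in section 2.6.1, a significant Time 1 interaction would count as support for Hypothesis 4 and be reported as a feature of the groups before the intervention. It could in fact be chance, selection of completers, or an early effect of one modality. A reader of the results could not tell these apart.

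**Working it through.** There is no power calculation to reproduce: "The sample size (*n* = 80) was determined pragmatically and based on operational feasibility", "with 40 participants per modality (20 men and 20 women in each; see Table 1". The split is consistent: 2 × (20 + 20) = 80.

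**Step 1. When each variable in Hypothesis 4 is measured at Time 1** (section 2.3.3 and Table 1)

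| Relationship | Predictor | Outcome | Wholly pre-exposure? |
|---|---|---|---|
| (a) coach style, needs | week 2 | week 2 | no |
| (b) needs, motivation | week 2 | week 2 | no |
| (c) motivation, lifestyle | week 2 | week 0 | no |
| (d) motivation, burnout | week 2 | week 2 | no |

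The count of wholly pre-exposure relationships is 0 of 4.

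**Step 2. Whether the arms differ by week 2.** Sections 2.4.2, 2.4.3 and 2.5 give the weekly content:
- Football or HIIT sessions: 2 × 120 = 240 minutes face-to-face, against 2 × 24 = 48 minutes on average by video.
- Nutrition: 30-minute talks plus counselling, against 5-minute capsules.
- Psychoeducation: group sessions of about 30 minutes, against capsules of about 5 minutes.

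The questionnaires therefore follow at least one week of clearly different delivery.

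**Step 3. What a Time 1 interaction could mean**
- *If Time 1 were truly pre-exposure:* each interaction is null. Four independent tests at 5% give 1 − 0.95⁴ = 0.185, an 18.5% chance of at least one false finding. A simulation of the interaction test (4,000 runs, 40 per arm, equal slopes of 0.3, two-sided 5%) rejected 4.3% of the time, close to nominal.
- *On the actual week-2 timing, (a), (b) and (d):* a real difference in slopes is possible. With one slope assumed at 0.3, the same simulation rejected 7.8%, 15.6% and 52.1% of the time for a second slope of 0.4, 0.5 and 0.7. Those rejections would be genuine, but they would be early effects and not baseline properties.
- *Relationship (c):* the lifestyle score precedes delivery, so delivery cannot have changed how motivation acts on it. A Time 1 interaction could come from chance, completer selection or an early shift in motivation scores. None of these is the moderation that Hypothesis 4 describes.

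**Step 4. Sensitivity of the comparison.** For two correlations with 40 per arm, the standard error of the Fisher z difference is √(2/37) = 0.2325. The difference detectable with 80% power is (1.96 + 0.84) × 0.2325 ≈ 0.651. If one arm has r = 0.30 (z = 0.3095), the other needs z ≈ 0.961, that is r ≈ 0.745. With an assumed 32 or 28 completers per arm, this rises to about 0.78 or 0.80. The limit is the same at week 13.

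The slopes, correlations and completer numbers are illustrative assumptions; the article gives none.

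**The case against.** The strongest reply is that the week-2 timing is deliberate and disclosed. Participants need some contact with the programme before they can rate a coach or their own motivation in it. Whether the modalities already differ at week 2 is a fair question, and section 2.6.1 calls moderation exploratory. The timing and the label both stand. But the exploratory label addresses sample size. It does not change a hypothesis that places the effect at baseline, nor a reading rule that treats a Time 1 interaction as support for it.

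Three stronger readings are tempting and are not supported.

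- *Baseline moderation is null by design, so any positive result is chance.* That requires pre-exposure measurement, which none of the four relationships has in full. Even a true baseline would not be strictly protected, because the analysis set is restricted to completers after randomisation, as section 2.6.1 concedes.
- *The false-positive risk is 18.5%.* That figure holds only if Time 1 were pre-exposure and the four tests independent. They share variables and participants.
- *Splitting the baseline models by modality wastes half the sample, so they must be pooled.* Section 2.6.1 does say "Separate models will be estimated for each intervention modality (face-to-face and semi face-to-face) and for each measurement occasion (baseline and post-intervention", but this serves Objective 1, which asks about associations within each modality. Hypothesis 4 uses interaction terms. The precision cost is real: for an assumed r = 0.30, tanh(0.3095 ± 1.96/√37) gives −0.01 to 0.56 at n = 40, and tanh(0.3095 ± 1.96/√77) gives 0.09 to 0.49 at n = 80. But exposure already differs by arm at week 2, and a modality covariate in a pooled model adjusts means, not slopes. Pooling against stratifying is a trade-off, not an error.

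**Conclusion.** The concern holds in this limited form: the baseline half of Objective 4 and Hypothesis 4 cannot be answered as written. Under the baseline label the interactions should be null apart from chance and completer selection. Under the actual timetable, (a), (b) and (d) are week-2 results that may carry an early modality effect, and (c) sets a week-2 predictor against an outcome recorded before delivery. It affects 4 of the 8 moderation tests (four relationships at two occasions).

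The conclusion about timing rests on section 2.3.3 and Table 1 alone. Only the rejection rates and detectable differences depend on assumed values. The point concerns exploratory analyses, and it is worth correcting because the correction changes what the trial may claim at almost no cost. Using week-2 scores as the starting point for change in burnout is a separate question that this point does not settle.

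**What to change.** - Remove the baseline claim from Objective 4 and Hypothesis 4, and rest the hypothesis on the week-13 interaction tests. Keep the completer-only caveat already in section 2.6.1 attached to them.
- If Time 1 interactions are reported for (a), (b) and (d), describe them as exploratory week-2 results after early exposure, and state that they do not count as baseline support for Hypothesis 4.
- Drop the Time 1 test of (c).
- In the moderation paragraph of section 2.6.1, replace the pre-intervention description of these data with the actual week of measurement.

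This needs no new data, and the Objective 1 models can stay as they are. The cost is a wording change and the loss of one set of exploratory tests as evidence for the hypothesis. It does not improve the low power of the week-13 tests, which the exploratory label must continue to cover.

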**Hypothesis** **5.**
*The psychoeducational intervention will achieve adequate acceptability, and participants will perceive a positive contribution in terms of motivation toward physical activity, psychological well-being, and psychological ill-being in both modalities.*

The development of this protocol will contribute to establishing methodological guidelines that, once examined, may guide future psychoeducational interventions in sports contexts, particularly those targeting sedentary and overweight adults, by providing a framework for the promotion of healthy habits and psychological well-being.

## 2. Materials and Methods

### 2.1. Design

A mixed-methods convergent parallel approach will be adopted [40] within the framework of a longitudinal comparative pragmatic clinical trial [41]. To examine changes and to compare delivery modalities, the participants will be randomly assigned to receive the intervention in either a face-to-face or semi face-to-face modality, with measurements at time 1 (baseline) and time 2 (post-intervention).

Quantitative analyses will include hierarchical multiple regression analyses, pre-post comparisons, and regression-based mediation and moderation analyses [42,43]. Additionally, the acceptability and perceived contribution of the intervention will be explored using a qualitative phenomenological approach [44] through a post-intervention focus group. The findings from the statistical analysis and the results of the phenomenological analysis will be integrated, allowing for a more precise understanding of the intervention’s evaluation, its perceived impact, and the acceptability of each modality.

Although this study does not constitute a controlled trial and does not include a no-intervention control group, to ensure methodological rigor and scientific transparency, it has been designed in accordance with the standard items of the SPIRIT 2013 Statement for clinical trial protocols [45] (see Supplementary Materials S1) and takes as a reference the elements of the Trials Registration Data Set (TRDS) [46] considered by the World Health Organization (WHO). In addition, the description of the intervention has been guided by the Template for Intervention Description and Replication (TIDieR) checklist [47] (see Supplementary Materials S2), with the aim of providing a comprehensive, transparent, and replicable account of the intervention components, delivery procedures, materials, and implementation context.

### 2.2. Participants and Sample Size

#### 2.2.1. Study Setting

The program will be carried out in Nuevo León, Mexico, in collaboration with the Tigres Football Club and the Autonomous University of Nuevo León. The psychoeducational activities will take place at facilities provided by the university (See Supplementary Materials S3).

The choice of the state of Nuevo León as the study setting is justified by its high combined prevalence of overweight and obesity—76.6% in 2022—higher than the national average of 76.2%, ranking first in the country [48,49]; this is taken together with the strong identity of the supporters of Club Tigres, one of the most popular teams in Mexican football [50].

